### Ethical and research governance approval

Ethical approval was received by the Office for Research Ethics Northern Ireland (ORECNI: 22/NI/0156), and research governance was obtained from all participating health boards in Northern Ireland, Scotland and England.

### Status and timeline of the study

The total duration of the study will be 45 months, including follow up at 6 and 12 months after randomisation for all participants, and at 18 months after randomisation for those participants recruited to the internal pilot. We will open the first site within five months and aim to have eight sites open within 22 months. The internal pilot will run during months 5–14. Following successful confirmation of recruitment rates, the internal pilot will move into the main study. The total recruitment period will last until month 25. There will be 3 months at the end for final data analysis, reporting and close-down.

We have chosen eight clinical sites across three UK countries (Northern Ireland, Scotland, and England) to maximise recruitment across a large population and improve the applicability of our results. The clinical sites cover a range of urban and semi-rural areas, and include areas with high levels of deprivation, a wide range of ethnicities and are culturally diverse. We will use a range of community settings to deliver the DESMOND-ID education programme. To be involved in the study, community ID or other appropriate healthcare professionals at the clinical sites must be prepared to participate in the DESMOND-ID training package and be prepared to deliver the intervention.

### Recruitment process

Recruitment between January 2023 and December 2024 will take a multi-pronged approach. Potential participants with ID and T2D will be identified via their community ID teams and associated services (including ID residential homes and ID-day centres/opportunities). While additional potential participants with a mild/moderate ID and T2D who might not be known to statutory ID services will be identified by primary care/general practices in each site using the Read Code system. Each ID clinical team will work with us to compile a list of those who have already been contacted to avoid duplication. Each community ID team and GP practice will send out an invitation letter, participant information sheet (PIS) and reply slip. This will be followed by a telephone call and those who agree will be referred to the study by the clinicians in the participating clinical sites who will undertake the initial screenings.

We will also run a social media campaign to advertise the study and help with further identification of potentially eligible participants. The study will also be advertised in settings where adults with ID attend (e.g., day centres and care providers). If a potential participant indicates their willingness to join the study, their contact details will be forwarded to the team. 

The community ID team/GP Practice/housing provider/other ID service provider will send the potential participant an initial invitation letter with a reply slip. The community ID nurses at each clinical site will telephone those who have not returned their reply slip to remind them and support them to make an informed decision about participating in the study. When reply slips are returned to the research team, a clinical research nurse will telephone the participant to arrange to visit and discuss the study with interested participants in the presence of a family or paid carer or spouse/partner/advocate as appropriate.

All potential participants will be screened against the inclusion and exclusion criteria. All screening data will be recorded onto the screening log. The outcome of the screening process and reasons for the non-recruitment of potentially eligible participants will be recorded on the My Diabetes and Me screening log.

We know that some adults with an ID and T2D will be living alone in their own home and may not have a carer to accompany them during the education programme, and we will not exclude those individuals from taking part in the study.

### Inclusion criteria

Participants will be eligible to participate in the study in accordance with the following criteria:

Mild/moderate ID as confirmed by health professional/medical recordsDiagnosed with T2DAged ≥18yearsHave sufficient English language skills to fully consider/give consent, and be able to speak and understand English to undertake the programme if allocated to the intervention.Living in the community.

### Exclusion criteria

Type 1 DiabetesSevere/profound IDDisplaying severe challenging behaviourAcute psychotic illnessLack mental capacity to give consent.

### Consent

Written informed consent from each participant with ID and T2D will be obtained by clinical research nurses and/or research associates before entry into the study. According to the UK Mental Capacity Act 2005
^
35
^ it is often wrongly assumed that all people with ID do not have the mental capacity to make decisions of their own. It must be assumed that an adult with an ID has the capacity until proven otherwise. Therefore, it is important that the person is given the information required in a user-friendly format to make an informed decision using reasonable adjustments. We plan to manage on-going consent including assessment of capacity to consent using the following steps.

The research team and clinical research nurses will receive study specific training at each site in how to assess capacity to consent and ensure informed consent is maintained throughout the project on a case-by-case basis. All participants will receive an easy read PIS and consent form with pictures and symbols to explain the purpose of the study and what is involved. The PIS and consent form will be prepared in collaboration with our PPI representatives. The research team and clinical research nurses will clearly explain the decisions to be made about joining the study, having bloods and anthropometric measurements taken, and completing questionnaires at several time points, and being randomised to either the intervention or TAU group. The research team and clinical research nurses will explain what is involved in participating in the DESMOND-ID diabetes education programme (time commitments) if randomised to that group or what will happen if randomised to the control group.

The study team will assess if the person can retain the information and weigh up the pros and cons of making the decision to participate in study, allowing for plenty of time to communicate with the person with ID/T2D and to check they can retain this information. Where needed, the research team and clinical research nurses will ask for a family member, carer, partner or advocate who is familiar with the communication needs of the person with ID/T2D to be present during the interview.

### Randomisation and treatment allocation

When informed consent has been obtained participants will be randomised by the Northern Ireland Clinical Trials Unit (NICTU) using a centralised randomisation system in a 1:1 ratio, with allocation concealed until the person joins the study. Randomisation will be completed by an appropriately trained and delegated member of the NICTU team. Participants will be allocated to the intervention or TAU group. Randomisation will be stratified by site. At the time of randomisation, each participant will be allocated a unique alphanumeric code which will be used throughout the study for participant identification. The research team will then ensure that the participant’s GP is informed of their participation in the study. Due to the nature of the intervention, it is not possible to blind participants to their allocated treatment.

### Study intervention

DESMOND/DESMOND-ID is based on a series of psychological theories of learning and education: Leventhal’s Common-Sense Theory (i.e. illness representation, illness beliefs
^
36
^), Dual Process Theory (process of learning
^
37
^), and Social Learning Theory (i.e. self-efficacy
^
38
^). The philosophy of the programme was founded on the empowerment of individuals living with diabetes, as evidenced in published work
^
39
^ and its development followed a systematic approach, guided by the MRC framework for developing and evaluating complex interventions
^
40,
41
^.

In My Diabetes and Me, the DESMOND-ID programme will be delivered face-to-face in a range of community settings over a period of 7 weeks to 6–8 adults with ID and T2D and their carer/partner/advocate in a group setting, with two booster sessions in subsequent months (1 and 3 months after the end of the weekly sessions). The education sessions will be delivered by two healthcare professionals in each site, who will receive 3 days of training in DESMOND-ID education programme, plus an additional day of training before delivery of the booster sessions. The healthcare professionals will also be allocated 3 days for preparation and supervision of the delivery of the intervention. Staff from the DESMOND-ID team will conduct several quality assurance checks at each site throughout the duration of delivery.

Week 1 of the programme focuses on carers/partners/advocates only with the aim of improving their understanding of T2D and how DESMOND-ID works along with their supporting role. In weeks 2–7, we encourage the adult with ID/T2D and their carer/partner/advocate to attend together if possible. These weeks focus on: introductions to ‘My story with T2D, My body and T2D; What is T2D; What does T2D do to your body; Food and blood sugar, Knowing what your blood sugar levels mean; Being active; Heart and circulation problems; Other T2D health problems; What can I do to keep healthy; Food and fats; Making healthier food choices; and Developing a diabetes health action plan’ (see
Table 1).

**Table 1. T1:** DESMOND-ID structured education programme session plan.

Week 1	Week 2	Week 3	Week 4	Week 5	Week 6	Week 7
Carers and advocates only session.	Welcome and introduction (25 mins)	Welcome back (20 mins)	Welcome back (20 mins)	Welcome back (20 mins)	Welcome back (20 mins)	Welcome back (20 mins)
	My story with diabetes (part 1) (15 mins)	My story with diabetes (part 2) (15 mins)	Knowing what your blood sugar levels mean (35 mins)	Heart and circulation problems: what can I do to keep healthy? (part 1) (40 mins)	Food and fats (35 mins)	Diabetes health action plan: what will I work on? (35 mins)
	My body and diabetes (20 mins)	What diabetes does to your body? (25 mins)	Break (15 mins)	Break (15 mins)	Break (15 mins)	Break (15 mins)
	Break (15 mins)	Break (15 mins)	Being active (40 mins)	Other diabetes health problems: what can I do to keep healthy? (part 2) (35 mins)	Making healthier food choices (40 mins)	Keeping my plan going (35 mins)
	What is diabetes? (35mins)	Food and blood sugar (35 mins)	What did I learn today? (10 mins)	What did I learn today? (10 mins)	What did I learn today? (10 mins)	Important questions and celebration of achievement (15 mins)
	What did I learn today and preparing for next week? (10 mins)	What did I learn today and preparing for next week? (10 mins)	What did I learn today and preparing for next week? (10 mins)	What did I learn today and preparing for next week? (10 mins)	What did I learn today and preparing for next week? (10 mins)	
	**Total duration:** 2 hours	**Total duration:** 2 hours	**Total duration:** 2 hours	**Total duration:** 2 hours	**Total duration:** 2 hours	**Total duration:** 2 hours

The DESMOND-ID programme has been adapted by lengthening the timings of the structured programme, simplifying the core concepts, and making greater use of pictorial representations (photos, pictures, symbols) to meet the learning needs of adults with ID. It also makes use of repetitious learning/interactive sessions, there is a strong focus on developing skills and promoting “self-efficacy” in food choices and increasing physical activity, with the involvement of carers to support the person with ID/T2D, using health action plans and goal setting which are reviewed each week, and emphasising celebration and fun.

The booster sessions will be delivered 1 and 3 months after the completion of the DESMOND-ID programme. Each booster session will also last 2 hours and will be delivered by the same trained educators. These sessions will explore how each adult with ID and T2D, and their carer/partner/advocate are implementing their health action plan and any potential barriers. Those in the DESMOND-ID group will also receive TAU, ensuring that they do not lose any treatments or care that are standard.

### Treatment as usual group

Adults with ID/T2D who are randomly allocated to the control group will receive TAU and a user-friendly book previously developed to support adults with ID to manage their T2D. TAU will be established at the start of the study and again at the end of the study. Adults in the control group will not be offered any form of diabetes group education. TAU for this population normally includes health centre visits every 3–6 months in which the person meets with their primary healthcare team. We will monitor TAU for this population across the different countries.

### Outcome measures

In both randomised groups, participants with ID and T2D will complete all questionnaires and study outcome measures at baseline, 6 and 12 months follow-up, and those in the internal pilot study will also be followed-up at 18 months.

### Lifestyle and demographic information

1.Living status - participants will be asked questions to determine their living status (where and who they live with, and any carer support they receive).2.Medical history - a health history questionnaire will be administered to determine any pre-existing medical conditions. In addition, current medication will be recorded including dosage and frequency. 

### Primary outcome measure

The primary outcome is change in HbA1c level (mmol/mol), from baseline to 6 months post-randomisation. The HbA1c blood test reflects average blood glucose levels over the last 2 to 3 months. HbA1c (mmol/mol) will be assessed by taking a venous blood sample from participants.

### Secondary outcome measures

A range of the secondary outcome measures will be measured to assess group changes and differences over time as specified in
Figure 1. These include:

**Figure 1. f1:**
[figure not shown]
Study Schematic Diagram (Internal Pilot/Main Study).

**
*Body Mass Index (BMI).*
** To calculate BMI, height (cm) will be measured to the nearest 0.1cm using Marsden HM-250P Leicester Portable Height Measure. Weight (kg) will be measured to the nearest 0.1kg using Seca 875 Flat Scales.

**
*Blood sampling.*
** Data will be reported on blood lipids (i.e. total cholesterol; low-density lipoprotein (LDL) cholesterol; and high-density lipoprotein (HDL) cholesterol); and estimated Glomerular Filtration Rate (eGFR).

**
*Blood pressure.*
** sSystolic (SBP) and diastolic blood pressure (DBP) will be measured using an OMRON M3 blood pressure monitor. Participants will be asked to rest in a chair for at least 5-minutes before assessment.

**
*Illness perception measured using the Illness Perception Questionnaire-Revised (IPQ).*
** The Illness Perception Questionnaire ([IPQ]
^
42
^) is a method of assessing cognitive representations of illness. The IPQ is a theoretically derived measure comprising five scales that provides information about the five components that have been found to underlie the cognitive representation of illness. The IPQ will be used to examine a participants’ understanding of diabetes (illness coherence score), perception of the duration of their illness (timeline score) and perception of their ability to affect the course of their diabetes (personal responsibility score).

**
*Depression measured using the Glasgow Depression Scale.*
** The Glasgow Depression Scale for people with a Learning Disability ([GDS-LD]
^
43
^) is a self-report questionnaire containing 20 items which ask a participant about their experiences in the previous week. Participants must select one from three possible answers: (1) never/no, (2) sometimes and (3) always/a lot, each being scored 0, 1 or 2. Total scores are calculated, ranging from 0 to 40.

**
*Health related quality of life measured using the EQ-5D-Y.*
** This EQ-5D-Y
^
44
^ is aimed at young people aged 8 years and older and is adapted directly from the EQ-5D-3L with simplified wording making it more appropriate for this population. It is a generic preference-based measure of health, which provides a description of health using five dimensions (mobility, self-care, usual activities, pain/discomfort and anxiety/depression each with 3 levels of severity. Responses can be converted to an overall utility score for the calculation of quality adjusted life years (QALYS).

**
*Health and social care service use and costs measured using the Modular Resource use Measure (ModRUM).*
** ModRUM
^
45
^ is a validated, concise, generic, measure designed to collect self-report data on the healthcare services people use in UK-based studies. The measure contains a set of core modules that can be expanded to ask participants for additional details by substituting ‘core’ questions for ‘depth’ questions.

### Intervention costs

Intervention costs will be recorded prospectively by the study team.

### Data analysis

The primary analysis will be conducted on all outcome data obtained from all participants as randomised and regardless of protocol adherence, i.e. intention to treat analysis according to their randomisation group. Per protocol analysis will also be carried out: patients who attended all 6 education programme sessions and at least one booster session. A detailed statistical analysis plan (SAP) will be developed. Baseline characteristics and follow-up measurements will be summarized as means and standard deviations, medians and inter-quartile ranges, or numbers and percentages, as appropriate. The difference between randomised groups in change from baseline at 6-months for HbA1c (mmol/mol) levels will be analysed using a t-test. Analysis will use a significance threshold of
*p* ≤ 0.05. Secondary analysis for the primary outcome using ANCOVA will adjust for baseline and site. The comparison of other continuous outcomes between the two groups will be investigated using analysis of covariance, adjusting for baseline/other covariates where appropriate or t-test. Dichotomous outcomes will be analysed using chi-square and logistic regression if adjustment for covariates is required. Any adjustment for covariates will be based on clinical input and pre-specified in the SAP. To ensure the quality of the data and trial, we have established a trial steering committee and an independent Data Monitoring Committee which consists of experts external to the trial.

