### Study sample

In total, 191 participants in each randomised group will have 90% power to detect a difference in means of 0.5% in HbA1c (mmol/mol) at 6 months. This 0.5% cut-off point is accepted in the diabetes community as being a minimal clinically important difference, ensuring that an effect of this size or greater will be seen as a meaningful indication of the effectiveness of the intervention
^
5
^. We assumed a standard deviation of 1.5%
^
31
^ and used a two-group t-test with a 0.05 two-sided significance level. Assuming a dropout rate of 15%, the sample size required is 450 participants (225 per group). This dropout rate is likely to be an overestimate because our feasibility study showed that <10% of recruited adults with ID dropped out
^
23
^ and other National Institute for Health and Care Research (NIHR) ID intervention studies have reported similar results
^
32,
33
^.

The current intention is to seek an excess of 30%–40% individuals within the ID and T2D population over this sample size who might be willing to take part in the study. Therefore, 585–630 adults with ID and T2D will be identified to provide some flexibility for those not meeting the criterion, refusals and dropouts. This 30%–40% is a generous estimate and is based on our feasibility study’s recruitment rates
^
23
^ and other diabetes and ID studies
^
34
^.

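### The per-protocol set is defined only by attendance at sessions that controls are never offered, so it has either no comparator or a non-randomised one that probably favours the intervention

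*Protocol article*

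**What the plan says.** The Data analysis section makes the primary analysis "i.e. intention to treat analysis according to their randomisation group". For the primary outcome it says: "The difference between randomised groups in change from baseline at 6-months for HbA1c (mmol/mol) levels will be analysed using a t-test". It then adds a second analysis set: "Per protocol analysis will also be carried out: patients who attended all 6 education programme sessions and at least one booster session". It gives no membership rule for the treatment-as-usual arm.

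Under Treatment as usual group the article says: "Adults in the control group will not be offered any form of diabetes group education".

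Under Study intervention, week 1 is for carers only. For the six sessions meant for participants, the text is: "In weeks 2–7, we encourage the adult with ID/T2D and their carer/partner/advocate to attend together if possible". Two boosters follow, one and three months after the weekly sessions. The Recruitment process section notes that some participants living alone "may not have a carer to accompany them during the education programme".

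The Process evaluation section (Table 2, dose delivered) shows that attendance lists are kept for each session.

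**The concern.** The rule selects on something that happens after randomisation, and in one arm only. Nothing observed among controls identifies those who would have attended all six sessions and a booster, so the matching group cannot be picked out there.

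Full attendance probably depends on carer support, general health and motivation. The article itself shows that carer support varies between participants. If those same factors are related to how HbA1c changes over six months, the comparison mixes the effect of the programme with differences between the people who complete it. A per-protocol result is easily read as the effect in people who attend. This definition cannot deliver that estimate.

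**Working it through.** **1. The plan's own figures.** The Study sample section says "In total, 191 participants in each randomised group will have 90% power to detect a difference in means of 0.5% in HbA1c" and "We assumed a standard deviation of 1.5"%, with a two-sided 0.05 t-test and 15% dropout. Solving the two-sample t-test for a standardised difference of 0.5/1.5 = 0.333 gives 190.1, rounded up to 191 per arm. Then 191/0.85 = 224.7, so 225 per arm and 450 in total. These figures reproduce and are not in question. The 0.5-point target and the 1.5-point SD are used below.

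**2. Who can be in the set.** The rule needs six sessions plus a booster. Controls are offered no sessions. Applied literally to both arms, the set holds 0 controls. A comparison exists only if controls are admitted without an attendance criterion.

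**3. Size of the selection effect with no true effect.** The article gives neither an attendance rate nor an attendance–outcome correlation, so these inputs are assumed:
- probability p of attending each session or booster: 0.85 or 0.90;
- each participant has a standard normal tendency to attend, L, which induces a latent correlation r of 0.3, 0.5 or 0.7 between sessions;
- L correlates ρ = 0.2 or 0.3 with improvement in HbA1c;
- the SD of change equals the planning SD of 1.5 points.

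A session is attended when √r·L + √(1−r)·e exceeds the cut-off that gives probability p, with e independent noise. A participant qualifies with all six sessions and at least one of two boosters. The bias is ρ × 1.5 × (mean of L among those who qualify). Simulation with 4 million participants per row gives:

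| p | r | Share qualifying | Mean L | Bias, ρ = 0.2 | Bias, ρ = 0.3 |
|---|---|---|---|---|---|
| 0.85 | 0.3 | 49% | 0.589 | 0.18 | 0.26 |
| 0.85 | 0.5 | 57% | 0.588 | 0.18 | 0.26 |
| 0.85 | 0.7 | 65% | 0.532 | 0.16 | 0.24 |
| 0.90 | 0.3 | 62% | 0.443 | 0.13 | 0.20 |
| 0.90 | 0.5 | 68% | 0.445 | 0.13 | 0.20 |
| 0.90 | 0.7 | 74% | 0.404 | 0.12 | 0.18 |

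The smallest bias is 0.2 × 1.5 × 0.404 = 0.121 and the largest 0.3 × 1.5 × 0.589 = 0.265. Against the 0.5-point target these are 24% and 53%. Between 225 × 0.49 = 110 and 225 × 0.74 = 166 intervention participants would qualify, before dropout.

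**4. Limiting cases.** With ρ = 0 the bias is zero. With a negative ρ the sign reverses. If sessions are attended independently (r = 0), the share is 0.85⁶ × (1 − 0.15²) = 37% or 0.90⁶ × (1 − 0.10²) = 53%. Full attendance is then pure chance, and the bias is again zero.

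**The case against.** - **It is supplementary.** Intention to treat is primary, and no progression rule, sample size or conclusion is tied to the per-protocol set. The economic model draws on the main 12-month trial analysis. This stands and limits the severity. A reader might infer that the trial's main conclusion is at risk; the article does not support that.
- **The SAP may settle it.** The article announces a detailed SAP, and how controls enter the set could be stated there. The ordinary reading is that the sentence defines adherence to the intervention and that controls count as adherent to usual care. This stands in part, and the absence of a control rule is not itself the point. The attendance rule is already fixed in the article, however, and no rule for controls can identify those who would have attended everything.
- **The direction is not proven.** The outcome is a change score, so stable differences in HbA1c level cancel. If full attenders start with better control, regression to the mean and less room to fall could work against the intervention. This stands. A reader might infer that the analysis must show benefit even if the programme does nothing, but the documents support only that this is the likelier direction.
- **The size is easily overstated.** It is tempting to take the 37–53% share from independent sessions and combine it with a bias that assumes one trait fully determines attendance. The two assumptions contradict each other, which is why the working uses a single model for both.
- **An instrumental-variable analysis has its own assumptions.** A count of the six sessions alone would ignore the week 1 carer session and the boosters, both of which could affect HbA1c. A minimum-attendance version assumes no benefit below the threshold. Both points stand and shape the fix.

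**Conclusion.** The point holds as a fault in a supplementary analysis. As written, the per-protocol rule gives either no comparator or a contrast of self-selected attenders with unselected controls. That follows from the text and needs no assumption.

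Bias towards the intervention is likely, not certain. Its size, about 0.12–0.26 HbA1c points with 49–74% of the arm qualifying, depends on assumed attendance, between-session correlation and attendance–outcome correlation, and on using the planning SD for change. It vanishes if attendance is unrelated to outcome. The plan should be changed, but the primary analysis stands.

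**What to change.** Make a complier-average causal effect analysis the adherence analysis:
- Use randomised arm as the instrument, adjust for baseline HbA1c and site, include all randomised participants, and handle missing outcomes as in the primary analysis.
- Measure attendance as the number of sessions including boosters (0 to 6 + 2 = 8), and add a version with a minimum attendance set in advance.
- State the exclusion restriction: allocation affects HbA1c only through the attendance counted. Say explicitly how the week 1 carer session bears on it.
- State that the minimum-attendance version assumes no benefit below the threshold.

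If the attendance-based per-protocol comparison is kept, say that all controls enter it and label it exploratory and non-randomised.

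The cost is a wording change in protocol and SAP and one extra model; attendance is already recorded. The interval will be wider. With one-sided non-adherence, the minimum-attendance estimate is the intention-to-treat difference divided by the share who comply. If the threshold were the present rule and 49–74% met it, estimate and standard error would both scale by about 1/0.74 = 1.4 to 1/0.49 = 2.0. The assumptions cannot be tested, but they are stated, and a zero effect of allocation still gives a zero estimate.
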